### 2.2. Outcomes

Determine normal values for the imaging biomarkers (elastance and microvascularization) in healthy lung parenchyma and within different healthy areas.Determine the values for the imaging biomarkers (elastance and microvascularization) in lung consolidation.Evaluate differences between the imaging biomarker values on healthy lung vs. consolidated lung.Evaluate differences between the imaging biomarker values of group 1 (BP) vs. group 2 (atelectasis). This would allow the establishment of a cut-off point for the etiological differentiation of lung consolidations.

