## Abstract

**Background:** Acute lower respiratory tract conditions are highly prevalent in paediatrics. Many of these conditions present as consolidations on imaging studies. One of the most common causes is bacterial pneumonia (BP), which requires an accurate diagnosis to implement the best treatment plan. Despite the fact that major guidelines constrain the use of invasive tests, chest X-ray (CXR) or blood tests are still routinely used for the diagnosis. In this regard, the introduction of lung ultrasound (LUS) signified an advancement in reducing the invasiveness of diagnosis. However, there are still situations where distinguishing between different aetiologies remains challenging, especially in the case of atelectasis. **Methods:** This is a prospective cohort study to assess the diagnostic accuracy of new non-invasive, quantifiable, and reproducible imaging biomarkers (lung elastance and microvascularization ratio) for differentiating BP from another major entity that causes the appearance of consolidation in imaging tests, atelectasis. It will be conducted at Sant Joan de Déu Hospital in Spain from June 2025 to June 2027. Firstly, imaging biomarkers will be measured in well-aerated lung tissue without consolidation to establish their values in healthy lung tissue, according to a predefined imaging acquisition protocol. Subsequently, the imaging biomarkers will be assessed in patients with confirmed lung consolidation by LUS (Group 1: BP; Group 2: atelectasis). **Results**: The study aims to determine whether there are statistically significant differences in the biomarker values in relation to the normal values and between the different etiological groups. **Conclusions**: The demonstration of the reliable diagnostic accuracy of these biomarkers could significantly reduce the need for invasive techniques and improve the therapeutic management of many patients with BP and other pulmonary conditions presenting with consolidation in imaging tests.

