## 2. Materials and Methods

### 2.1. Study Design

This is a prospective cohort study aimed at validating the effectiveness of two novel non-invasive imaging biomarkers. It will be conducted at Sant Joan de Déu Hospital, a tertiary children’s hospital in Barcelona (Spain). The recruitment and follow-up period is planned from June 2025 to June 2027. As previously mentioned, the imaging acquisition protocol will guide the various phases of the study (Figure 2):

Phase 1: Measurement of elastance and microvascularization ratio in well-aerated (non-consolidated) lung tissue. Patients without pulmonary consolidation will be included in this phase.

Phase 2: Measurement of elastance and microvascularization ratio in consolidated lung tissue. Patients with confirmed pulmonary consolidation via LUS (even if the initial detection was through other imaging techniques) will be recruited. Patients will then be classified into two groups based on the final diagnosis:Group 1: BPGroup 2: Atelectasis

The final BP diagnosis will be made by a clinical expert using the BTS definition for CAP and the CDC criteria for VAP. This includes compatible clinical symptoms (such as fever, cough, tachypnea, and shortness of breath), abnormal auscultation patterns, LUS findings (according to Section 2.4.1), and blood test abnormalities suggestive of bacterial infection (leukocytosis, neutrophilia, CRP > 50 mg/L, and/or PCT > 1 ng/mL). Atelectasis will be diagnosed in patients with respiratory distress, without blood test abnormalities suggestive of bacterial infection (CRP < 50 mg/L and PCT < 1 ng/mL), and compatible LUS findings (according to Section 2.4.1), which resolve after increasing ventilatory support and performing respiratory physiotherapy.

For the differential diagnosis of both entities, respiratory sample cultures will not be considered, as false negatives may occur (in the context of BP) or colonizing organisms may be detected (even in cases of atelectasis).

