### 2.7. Statistical Analysis and Sample Size

To determine the normal reference values of elastance and microvascularization ratio in the healthy lung, measures of central tendency (mean and median) and dispersion (standard deviation, interquartile range) will be calculated for both elastance and microvascularization variables. The distribution of the variables will be assessed using the Shapiro–Wilk test to determine if the data follows a normal distribution. If the variables follow a normal distribution, the standard approach will be applied using the Faulkenberry-Weeks approach implemented in the tolerance R package. If the variables deviate from normality, non-parametric bootstrap methods will be used to estimate the tolerance intervals. Variability of the biomarkers across different patient subgroups (e.g., by sex or age) will be explored using analysis of variance (ANOVA), provided the assumptions of ANOVA are met. If assumptions are not met, permutation tests will be applied. A *p*-value of less than 0.05 will be considered statistically significant for all statistical tests. A sample of 60 subjects is considered sufficient to obtain 90% tolerance intervals at 95% confidence with a 5% error in tolerance and a 2.5% error in confidence [30].

Subsequently, to establish differences in the values of the imaging biomarkers among the different groups (BP, atelectasis, and normal baseline), analysis of variance (ANOVA) will be performed. In the event of finding significant differences, post-hoc analysis will be conducted using Tukey’s method. If the conditions for the applicability of ANOVA are not met, a permutation test will be applied. The sample size for the ANOVA test is calculated using the method proposed by Cohen. According to this method, the test effect size is the ratio of the sum of squares between groups to the total sum of squares. Cohen suggested a value of 0.25 as a medium effect size. The sample size is calculated using the pwr R package, which gives a sample size of 53 subjects per group required to detect a medium effect size with 80% power and three groups [31].

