## 3. Limitations

One of the main limitations of this project is that it is a single-centre study. However, it is a tertiary paediatric hospital that handles a high volume of patients, making the sample potentially large and representative at the population level. A potential selection bias in Phase 1 may arise from evaluating imaging biomarkers in patients who present to the hospital for reasons unrelated to pulmonary consolidation. This could limit the generalization of normal value results to the general population. Another limitation of the study is the potential for artifacts in biomarker measurements due to the presence of air in non-consolidated pulmonary tissue. If this issue occurs, it cannot be addressed by adjustments to the biomarker acquisition technique and would affect Phase 1 of the study. In this phase, it may be concluded that SWE and SMI are not reliable pulmonary diagnostic tools in the absence of consolidation. This could serve as a key preliminary finding of the study. In contrast, in Phase 2, where consolidated (non-aerated) pulmonary tissue is being assessed, the presence of air is unlikely to cause measurement artifacts. Another relevant aspect is the potential inter-observer variability, although this is not included among the objectives of the ELASMIC study, and thus, imaging biomarkers will be acquired by a single examiner. However, given that the examiner is a highly qualified professional trained in LUS image acquisition, the study assumes minimal inter-observer variability (the differences in measurements taken by another observer are negligible and clinically insignificant) and minimal intra-observer variability (the differences in measurements taken by the same examiner are negligible and clinically insignificant). Another limitation, which also represents a strength due to its innovative potential, is the use of diagnostic techniques that are not conventionally employed for evaluating lung tissue. In this regard, significant differences in the manual pressure exerted by the operator with the transducer could modify the measured results. Therefore, it will be essential to apply minimal pressure and verify the stability of the color map prior to the acquisition of the biomarkers.

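### The study is presented as validating the biomarkers, but its cut-off would be derived and judged in the same single cohort, which is a derivation design

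*Protocol article*

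**What the plan says.** Section 2.1 states the purpose: "This is a prospective cohort study aimed at validating the effectiveness of two novel non-invasive imaging biomarkers". The Abstract puts it in terms of accuracy: "This is a prospective cohort study to assess the diagnostic accuracy of new non-invasive, quantifiable, and reproducible imaging biomarkers". Its conclusion begins: "The demonstration of the reliable diagnostic accuracy of these biomarkers could significantly reduce the need for invasive techniques".

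The Introduction says that normal values of these biomarkers, and the role of the tests, have not yet been evaluated in children. It adds that nothing has been published on the microvascularization ratio in these lesions. For elastance it cites one adult study: 2.51 (SD 1.14) kPa in atelectasis and 19.98 (SD 15.59) kPa in pneumonic consolidation.

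Section 2.2 names the route to a threshold, as a consequence of comparing group 1 with group 2: "This would allow the establishment of a cut-off point for the etiological differentiation of lung consolidations". Section 2.1 describes one phase 2 cohort: "Patients will then be classified into two groups based on the final diagnosis". Section 3 concedes: "One of the main limitations of this project is that it is a single-centre study". It does not mention that the cut-off will be untested in new children.

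Section 2.7 covers tolerance intervals, ANOVA with Tukey's method and permutation tests. The ANOVA sample size rests on "Cohen suggested a value of 0.25 as a medium effect size", "which gives a sample size of 53 subjects per group required to detect a medium effect size with 80% power and three groups". The section gives no rule for choosing the cut-off.

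**The concern.** Validation requires a rule fixed before the data that test it. Here the rule does not exist until the phase 2 data are in, and the only children available to judge it are those who supplied it. The stated purpose and the design do not match.

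The practical risk is optimism. A threshold chosen because it separates these particular children best also fits their chance variation, so its apparent sensitivity and specificity exceed what new children would show. The Discussion links the results to updated diagnostic protocols and to fewer empirical antibiotics. A threshold presented as validated could be adopted on accuracy that it does not have.

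**Working it through.** **1. The design, read across sections.** Prior paediatric cut-off: none (Introduction). Source of the cut-off: BP versus atelectasis in phase 2 (2.2). Number of phase 2 cohorts: one, at one hospital (2.1, Section 3). Second or hold-out sample: none described. Stated purpose: validation and diagnostic accuracy (2.1, Abstract). The first four describe derivation; the fifth does not match them.

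**2. The plan's own figure.** For a one-way ANOVA with k = 3, Cohen's f = 0.25 and alpha = 0.05, the noncentrality is λ = k·n·f². At n = 53, λ = 3 × 53 × 0.0625 = 9.94 on 2 and 156 degrees of freedom, and power is 0.805. At n = 52 it is 0.797. The stated 53 per group is reproduced, with 0.25 read as Cohen's f.

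**3. The size of the optimism.** Let J = sensitivity + specificity − 1. For a cut-off c above which BP is called, true J(c) = F_atelectasis(c) − F_BP(c), where F is the distribution function in each group. Optimism = apparent J(c) in the sample − true J(c) at the same c.

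Inputs from the protocol:
- 53 per group
- the adult elastance means and SDs

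Assumptions, not in the protocol:
- c maximises J in the sample (Youden rule)
- equal-variance normal values with standardised difference d, for the generic rows
- lognormal, gamma or normal shapes matched to the cited mean and SD, for the elastance rows

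Each row is the mean of 6,000 simulated studies. Small discrepancies are rounding.

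| Setting | AUC | Apparent J | True J | Optimism (points) |
|---|---|---|---|---|
| d = 0.25 | 0.570 | 0.191 | 0.084 | 10.7 |
| d = 0.5 | 0.638 | 0.276 | 0.178 | 9.8 |
| d = 0.61 | 0.667 | 0.314 | 0.219 | 9.5 |
| d = 1.0 | 0.760 | 0.447 | 0.363 | 8.4 |
| d = 1.5 | 0.856 | 0.597 | 0.531 | 6.7 |
| d = 2.0 | 0.921 | 0.726 | 0.667 | 5.9 |
| d = 3.0 | 0.983 | 0.895 | 0.853 | 4.2 |
| Cited elastance, lognormal | – | 0.940 | 0.906 | 3.4 |
| Cited elastance, gamma | – | 0.870 | 0.832 | 3.7 |
| Cited elastance, normal | – | 0.832 | 0.809 | 2.3 |

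A second simulation of the same set-up gave 10.0, 8.4 and 7.0 points at d = 0.5, 1.0 and 1.5, and 3.3 for lognormal elastance. Simulation error is therefore a few tenths of a point.

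The row d = 0.61 ties to Section 2.7. With three groups and f = 0.25, the two extreme means lie furthest apart when the third is midway. Then f = d/√6, so d = 0.25 × 2.449 = 0.61. The effect size used for planning thus implies modest separation, where optimism is large; the cited elastance data imply strong separation, where it is small.

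**4. Split between the measures.** At d = 0.5 the excess is 5.0 points on sensitivity and 4.8 on specificity; at d = 1.0 it is 4.3 and 4.1; at the lognormal elastance values it is 1.7 and 1.7.

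**5. Spread in a single study.** These are averages. At d = 1.0 the 5th to 95th percentile of optimism runs from about −4 to +20 points.

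**6. Contrast.** With the cut-off at the midpoint of the two group means, mean optimism at d = 0.5 to 2 is 0.1 to 0.6 points. The bias comes from the search for the best threshold.

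**The case against.** - **No cut-off rule is stated, and Section 2.7 does not commit to reporting sensitivity and specificity at the cut-off.** This stands, so the size is conditional. A reader might infer that the reported sum will be 7 to 10 points too high. The documents do not support that without condition: it needs a sample-maximised cut-off and modest separation, and for the one biomarker with figures in the protocol the result is 2 to 4 points.
- **The bias does not attach to every accuracy statistic.** This stands. The Introduction states the expected direction for each biomarker, so a single-marker AUC in that direction involves no search, and a midpoint cut-off is nearly unbiased.
- **At the cited elastance values the bias is below sampling error.** This stands for elastance. At a sensitivity of 0.80 with 53 children the standard error is √(0.8 × 0.2/53) = 5.5 points, against 1 to 2 points of optimism. For the microvascularization ratio no separation is given, so a larger bias cannot be excluded.
- **An analysis plan that is not shown may hold a bootstrap or cross-validation correction.** This stands, and the lack of one in the article is not the fault raised. Such a correction would still not turn one derivation cohort into a validation.
- **The wording is softer than it looks.** Section 2.1 speaks of validating the biomarkers' effectiveness, not a threshold; the Abstract's conclusion is conditional; and the Introduction admits that paediatric evidence is lacking. This moderates the point. The stated purpose is still validation together with diagnostic accuracy, and Section 3 gives no warning about an untested cut-off.

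**Conclusion.** The point holds as a mismatch between stated purpose and design: validation is announced, while the cut-off would be established in the only cohort available to judge it. That follows from the text and depends on no simulation.

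The numerical consequence is conditional on 53 per group and a cut-off chosen to maximise sensitivity plus specificity. The sum is then too high on average by about 2 to 4 points at the cited adult elastance values, if those carry over to children, and by about 7 to 10 points for d of about 0.5 to 1.5. The latter range is an assumption, and for the microvascularization ratio any figure is. The point should be corrected because it changes what the study may conclude; it does not undermine the group comparisons in Section 2.7.

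**What to change.** In Section 2.1, describe the study as deriving a candidate cut-off. In Section 2.2 and the Abstract, restrict the conclusion to a candidate cut-off that needs external validation. If sensitivity and specificity are reported at that cut-off, give them after bootstrap optimism correction that repeats the cut-off search in every resample, with an interval for the cut-off itself.

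The cost is a few changes of wording and a few lines of analysis code, with no additional patients. The downside is that the reported accuracy becomes slightly less favourable.

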### 2.3. Inclusion and Exclusion Criteria

Inclusion: children under 18 years of age admitted to the hospital without pulmonary pathology will be recruited for developing phase 1 of the study. Subsequently, children under 18 years of age admitted to the PICU with lung consolidation present on admission or developed during their stay will be recruited for developing phase 2 of the study. Signed acceptance of informed consent must be obtained from the children’s legal guardians.

Exclusion: children with a history of pulmonary (asthma, bronchopulmonary dysplasia, pulmonary fibrosis, etc.), oncological, or cardiac disorders, those in an immunosuppressed state, or those in end-of-life care will be excluded. This aims to reduce the possibility of introducing artifacts in the results due to the inclusion of patients with a potential baseline alteration of the biomarkers being studied. Additionally, patients participating in other clinical trials, as well as those who refuse to sign the informed consent form or withdraw consent later, will also be excluded from the study.

### 2.4. Imaging Acquisition Protocol

The LUS image acquisition protocol was developed to characterize and identify lung consolidation, as well as to integrate SWE and SMI lung measurements. This aims to standardize imaging procedures and reduce operator variability. The study will use a high-resolution linear ultrasound device (Aplio A500 Canon™; Tokyo, Japan) with an acoustic frequency of 7–14 MHz. If the linear probe does not allow visualization of up to 3 cm of pulmonary tissue depth (likely due to significant adipose tissue in the exploration area), a convex probe with a 5 MHz frequency will be used. This situation is expected to be exceptional, as we are evaluating paediatric patients, in whom pulmonary tissue is typically well visualized with the linear probe. Therefore, the collected data will be evaluated in a combined manner without distinguishing between the probes used. The patient will be evaluated in a supine position. In case of impossibility, the assessment will be conducted in a seated position.

#### 2.4.1. Lung Ultrasound Imaging Acquisition

LUS evaluation will be performed at the bedside, adhering to standard clinical practice. Lung consolidation will be identified by liver-like images or parenchymal images within the lung tissue with dynamic or non-dynamic bronchogram, anfractuous edges, and “shred” signs.

The LUS findings of BP include:Disruption of the pleural lineHypoechoic consolidation with dynamic and arborizing air bronchogramPerilesional B-line enhancements.

The LUS findings of atelectasis include:Hypoechoic consolidation with non-dynamic and parallel air bronchogramPossible loss of pleural movement adjacent to the consolidation.

#### 2.4.2. Lung Shear Wave Elastography Acquisition

Tissue elastance will be measured using lung SWE through an intercostal window, minimizing the manual pressure applied by the transducer. The SWE ‘Multi’ mode (Real-Time Shear Wave acquisition) will be activated, triggering a dual screen (TwinView), where the elastance map will be displayed on the left and the propagation map on the right (Figure 3). A colored box will be placed 1 cm from the capsule on the elastance map (with an elastance scale set at 40 kPa). Subsequently, a circular Region of Interest (ROI) of 10 mm (size 5 on our device) will be selected, with a measurement depth limited to a maximum of 5 cm. Measurements will preferably be taken in areas with homogeneous color on the elastance map and with shear wave propagation as parallel as possible. Of all the measurements taken, the two with the lowest standard deviation and an interquartile range (IQR) < 0.3 will be selected, and their mean value will be used for inclusion in the final statistical analysis.

#### 2.4.3. Superb Microvascular Imaging Acquisition

For the study of tissue microvascularization, the transducer will be kept perpendicular to the skin, using the same intercostal window without modifying the patient’s position. The microvascularization ratio measurement will be performed using SMI within the colored box previously defined for lung SWE measurement (Figure 4). The SMI Doppler mode will be activated, along with the ‘Vascular Index’ tool, selecting a velocity scale of 0.9 m/s. A rectangular ROI (15 × 10 mm) will be selected at a maximum depth of 5 cm. Microvascularization results will be expressed as a percentage.

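### Elastance is analysed as the mean of two readings, but no rule says how many SMI readings are taken or how they are combined

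*Protocol article*

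**What the plan says.** Sections 2.4.2 and 2.4.3 of the protocol article describe the two biomarkers in parallel and at similar length.

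- **Elastance (2.4.2).** From all readings taken, "the two with the lowest standard deviation and an interquartile range (IQR) < 0.3 will be selected, and their mean value will be used" in the analysis.
- **Microvascularization ratio (2.4.3).** The section fixes the probe angle, window, Doppler mode, index tool, velocity scale, region size (15 × 10 mm) and maximum depth (5 cm). It states that "The microvascularization ratio measurement will be performed using SMI within the colored box previously defined for lung SWE measurement" and ends with "Microvascularization results will be expressed as a percentage". It gives no number of readings, no rule for selecting or averaging them, and no quality criterion.
- **Sample size (2.7).** One calculation serves both biomarkers. It starts from "Cohen suggested a value of 0.25 as a medium effect size" and arrives at "a sample size of 53 subjects per group required to detect a medium effect size with 80% power and three groups". The significance rule is "A *p*-value of less than 0.05 will be considered statistically significant for all statistical tests".
- **Repeatability (3, Limitations).** A single examiner acquires all images, and the study assumes "minimal intra-observer variability (the differences in measurements taken by the same examiner are negligible and clinically insignificant". The only support offered is the examiner's training.
- **Prior data (1, Introduction).** The authors report that nothing has been published on this ratio in these lesions, and that paediatric normal values are not available for either biomarker.

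**The concern.** The two biomarkers have equal standing in every outcome of section 2.2, including a cut-off to separate bacterial pneumonia from atelectasis. For one of them the text fixes how the analysed value is formed from the readings. For the other it does not.

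That leaves two possibilities. If one SMI reading is taken, all of the reading-to-reading noise within a child goes into the analysis. Such noise shrinks the standardised difference between groups, blurs any cut-off and widens the normal limits. If several readings are taken without a rule, the single examiner decides which value is recorded. That is worse, because the choice can depend on the value or on the suspected diagnosis.

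The assumption of negligible intra-observer variability would make the issue vanish, but it has no data behind it. It also sits badly with the rest of the article: Table 1 classes SMI as dependent on the operator, the Limitations section says that transducer pressure could alter results, and averaging two elastance readings would add little if repeats hardly differed. Without stored repeats the study cannot test the assumption for SMI. A null SMI result would then be hard to interpret, since absence of a difference and noisy measurement could not be told apart.

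**Working it through.** **Inputs from section 2.7:** three groups, f = 0.25, 80% power, alpha 0.05, 53 per group.

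**Input assumed:** the single-reading intraclass correlation (ICC), meaning the share of variance in one reading that lies between children. The documents give none. The range used is 0.5 to 1.0, where 1.0 corresponds to the protocol's own assumption of negligible variability.

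**Step 1: reproduce the stated figure.** One-way ANOVA power comes from the noncentral F distribution with 2 and 3n − 3 degrees of freedom and noncentrality λ = 3·n·f². Solving for 80% power gives n = 52.40, rounded up to 53. At n = 53, λ = 159 × 0.0625 = 9.94 and power is 80.5%. The stated 53 is reproduced. The number of readings per child does not enter this calculation.

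**Step 2: effect of averaging m readings.** With independent errors, the variance of the mean relative to one reading is

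v = ICC + (1 − ICC)/m.

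If f = 0.25 is taken to hold for a single reading, the effect size for the mean is 0.25/√v, and λ = 9.94/v.

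| Assumed ICC | v, m = 3 | f, m = 3 | λ, m = 3 | Power, m = 1 | Power, m = 2 | Power, m = 3 |
|---|---|---|---|---|---|---|
| 1.0 | 1.000 | 0.250 | 9.94 | 80.5% | 80.5% | 80.5% |
| 0.9 | 0.933 | 0.259 | 10.65 | 80.5% | 82.6% | 83.3% |
| 0.8 | 0.867 | 0.269 | 11.47 | 80.5% | 84.7% | 86.1% |
| 0.7 | 0.800 | 0.280 | 12.42 | 80.5% | 86.8% | 88.8% |
| 0.5 | 0.667 | 0.306 | 14.91 | 80.5% | 90.8% | 93.8% |

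The m = 2 column corresponds to parity with elastance.

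**Step 3: sensitivity to the scale of f.** If f = 0.25 is instead taken to describe error-free values, the effect size is 0.25·√(ICC/v). Power at 53 per group for one versus three readings is then 75.9% versus 79.0% (ICC 0.9), 70.6% versus 77.1% (0.8), 64.4% versus 74.7% (0.7) and 49.3% versus 67.6% (0.5). The article does not say which scale it means. The first is the natural reading of a generic effect size applied to the variable that is analysed.

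**Step 4: limits of the calculation.** Step 2 assumes independent errors. Repeats taken in the same box and window share any error from placing them, and that part does not average out. If the ICC counts such error as noise, the gains above are upper limits. Variation between children is not reduced at all, so the gain levels off after two or three readings.

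**The case against.** The strongest objection is that the article never says that only one SMI reading is taken. Section 2.4.2 also speaks of one region of interest and then refers to several measurements, so singular wording proves little. A journal article may also leave replicate rules to the full protocol. This stands in part: a reader might infer that the ratio definitely rests on one reading, and the text does not support that. What remains is that two parallel paragraphs, equally detailed, fix the rule for one biomarker and not for the other.

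A reader might also infer that the study is underpowered for SMI, or that using one f for both biomarkers is a mistake. Neither follows. The value 0.25 is Cohen's generic medium effect, not derived from the variance of either biomarker, and it can be read as already including measurement noise. The 53 per group is correct for the stated inputs.

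It is tempting to argue from the physiology of a flow signal that SMI must vary from moment to moment. The documents contain nothing on this, so the point does not rely on it.

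Finally, under the protocol's own assumption the gain is nil. That is true at an ICC of 1.0, but the assumption is unsupported, and repeats are what would test it.

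**Conclusion.** The point holds as a weakness in how the SMI value is fixed, not as an error in a stated figure. The microvascularization ratio has no repeat or combination rule where elastance has one, and the plan offers no way to check the repeatability that it assumes.

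The benefit of three readings over one depends wholly on an assumed ICC: nothing at 1.0, about 3 percentage points of power at 0.9, about 6 at 0.8, about 8 at 0.7 and about 13 at 0.5. This takes f = 0.25 on the single-reading scale and independent errors. If several readings are already taken, the power gain does not apply as calculated, but the need for a rule that removes the examiner's choice does.

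The change is worth making because it is cheap, an unselected mean should not reduce power, and it yields a within-child standard deviation for a biomarker that has none.

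**What to change.** In section 2.4.3, state that a fixed number of SMI readings (for example three) is taken in the same box and window without moving the patient, and that their mean is the value analysed in both phases. State that no reading is selected or dropped because of its value. Store each reading separately so that the within-child standard deviation can be reported and the repeatability assumption in the Limitations section checked.

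With three readings the cost is slightly longer scanning in the same session, by the same examiner, and two more database fields. No extra children are needed, and the sample size in section 2.7 does not have to change.
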